### 2.6. Sample Size

Initially, we computed a sample size of 152, given a power of 0.8, an alpha level of 0.05 and inferring functioning according to clinical remission data [28]. To our knowledge, functioning as a main outcome for physical exercise in depression has not set a precedent to guide our calculations. Thus, we computed a Cohen’s d effect size of 0.5 to make estimations more reliable. An expected drop-out rate of 20% was set, which resulted according to the initial design in two arms of 76 subjects each. However, during the cocreative process of the intervention, it was discussed whether motivational messages of the app would mask the effect of the group sessions on the outcomes of the study. Therefore, it was decided to include a third study arm to assess the intervention without motivational elements triggered by the app. We increased the sample size by adding 20 participants, which will be distributed into the two experimental groups, leaving us with a sample size of 172.

### 2.7. Recruitment

The recruitment period will extend over 12 months and all participants will be given a smart band that will be free to use together with free access to the app after study completion.

The resources and strategies for identifying and recruiting potential subjects will include: (1) Sending a monthly newsletter to clinical staff in adult inpatient and outpatient wards to keep IDEA in mind. (2) Attending regular clinic meetings. (3) Posting leaflets or posters with a brief overview of IDEA in each clinic room at the trust. (4) Keeping in close contact with clinicians in the trust (outpatient, inpatient, and primary services) to make sure everyone has ongoing awareness and knowledge of the process. (5) Giving an incentive for trainee clinicians such as research ‘tokens’ for psychiatry training portfolio depending on the number of patients referred.

### 2.8. Assignment of Interventions: Allocation

During the baseline assessment, participants will be registered individually in the IDEApp web-based platform, which will randomly assign them to one of the three conditions while maintaining the following distribution:Intervention A: participants receiving the intervention and motivational messages (48 participants; 27.9% of the sample).Intervention B: participants receiving the intervention and no motivational messages (48 participants; 27.9% of the sample).Control group: using the smart band without motivational messages (76 participants; 44.2% of the sample).

When subjects enter the study, they will be allocated to whichever condition is furthest from the expected percentage of subjects allocated. This allocation system will allow us to guarantee that all groups will have an even distribution at baseline irrespective of the number of participants.

All participants will be identified with a computer-generated random number that will be paired with a 9-digit identification number.

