### 2.10. Implementation

Allocation and intervention assignment will be automatically generated by the IDEApp web-based platform once participants are registered in the system by study staff. A study psychologist will enrol participants in the trial after baseline assessment.

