## 6. Discussion and Conclusions

This project is subject to some limitations. First, participants who exercise regularly prior to the study inclusion may result in a confounding factor. Second, the physical assessment includes Body Mass Index as a measure of obesity to ensure that the morbidly obese are not put at risk by exercising. However, this does not exclude sarcopenic obesity, which includes normal weight, hence normal BMI but low muscle mass percentage. The usage of a body fat calliper and asking for a blood count looking for cholesterol levels would help make sure that people with sarcopenic obesity are not put at risk. Third, we assume that our sample will include subjects with adjustment disorders, including complicated grief where both time from the event and cultural issues play a sensible role regarding improvement. This may emerge as a confounding factor, and we should trust random assignment to handle it. Finally, introducing a new technology such as a wearable device can alter participants’ default behaviour; thus, the measurements may not accurately reflect the activity that they would normally perform under non-experimental conditions.

On the other hand, we introduce novel highlights such as using a transdisciplinary approach, performing the recruitment based on symptoms; the inclusion of personalised medicine, guaranteeing that every participant will receive a tailored prescription of exercise; a transdisciplinary team, joining mental health professionals with physical medicine and rehabilitation specialists; the creation of a brief intervention, comprised of one month to promote adherence; a blended therapy, combining a group intervention with IDEApp and the use of a smart band and promoting a behavioural change that might last longer, and finally evaluating functionality outcomes, providing us with more reliable and ecological outcomes.

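### The allocation rule as stated contains no random element between control and programme, so the primary contrast is about 96% to 100% predictable from past counts

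*Protocol article*

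**What the plan says.** Protocol article, section 2.8, says the participant is registered in the platform, "which will randomly assign them to one of the three conditions while maintaining the following distribution". The targets are 48 (27.9%) for Intervention A, 48 (27.9%) for Intervention B and 76 (44.2%) for control.

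The same section then gives the mechanism: "When subjects enter the study, they will be allocated to whichever condition is furthest from the expected percentage of subjects allocated". It states no probability, list, block or seed. The only random number it mentions is the participant's identification code.

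On timing, section 2.8 says "During the baseline assessment, participants will be registered individually in the IDEApp web-based platform", and section 2.10 says that registration by study staff generates the allocation. Section 2.10 adds: "A study psychologist will enrol participants in the trial after baseline assessment".

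On access, section 2.9 allows one researcher in charge of the evaluation to see whether a participant is in control or intervention, but not A versus B.

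Section 2.5.1 makes A and B combined versus control the main comparison. Section 6, on adjustment disorder and complicated grief as possible confounders, says "we should trust random assignment to handle it".

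**The concern.** Section 2.8 calls the assignment random and then describes a rule that depends only on how many people each arm already has. Such a rule keeps arm sizes on target, but it supplies no chance mechanism between control and programme.

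Two things are at stake. First, concealment: if the next assignment follows from past ones, anyone who knows the past placements can work it out without looking at the platform. Secondly, the basis for inference: section 6 trusts random assignment to deal with confounders that the trial neither excludes nor stratifies on in the published text. A rule that balances counts does not give that protection. The exposed contrast is the primary one.

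**Working it through.** **Inputs.** Targets of 48/172, 48/172 and 76/172, the allocation rule and the total of 172 come from section 2.8. The control-versus-intervention view of placements comes from section 2.9, and the primary contrast from section 2.5.1.

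**The plan's own figures.** 48/172 = 27.9%, 76/172 = 44.2%, and 48 + 48 + 76 = 172. These reproduce.

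**Readings of the rule.** Let *t* be an arm's target fraction, *c* its current count and *N* the number already allocated. The next entrant goes to the arm with the largest value of:

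1. percentage shortfall: *t* − *c*/*N* (with *c*/*N* taken as 0 at the start);
2. expected-count shortfall: *t*(*N* + 1) − *c*;
3. unfilled share of target, that is, the lowest *c*/*t*.

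**First steps by hand, reading 2.**
- Entry 1: A and B 0.279, control 0.442, so control.
- Entry 2: A and B 0.558, control 0.884 − 1 = −0.116, so a programme arm.
- Entry 3: the unused programme arm 0.837, control 1.326 − 1 = 0.326, so programme.
- Entry 4: A and B 1.116 − 1 = 0.116, control 1.767 − 1 = 0.767, so control.

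The only open question in these four steps is whether A or B comes first.

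**All 172 entries, by simulation with exact fractions and random tie-breaks.** The second column counts entries where control ties with a programme arm, so that the primary contrast is open.

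| Reading | Control/programme ties | Determined by past counts | Entries with any tie |
|---|---|---|---|
| Percentage shortfall | 3 | 169/172 = 98% | 48 to 51 |
| Expected-count shortfall | 0 | 172/172 = 100% | 48 |
| Share of target filled | 4 to 8 (mean about 6.7) | about 165.3/172 = 96% | 52 |

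All three readings end at exactly 48/48/76. Under reading 2 only one control/programme sequence is possible.

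**What an observer can do with the section 2.9 information.** Knowing only the running control and programme counts, without the A/B split, an observer guesses on average 99.2% of assignments correctly under reading 1 and 98.2% under reading 3. Under reading 2 the sequence is fixed. With simple randomisation at the same ratio, the best guess is always programme, which is right 96/172 = 55.8% of the time.

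**Readings that do not fit the text.** Distance in either direction would put all 172 in control, against the stated 48/48/76. Most places left against the final target would put the first 28 entrants in control and then leave 72 to 88 open entries, but it fails the section's claim that the distribution holds at any sample size.

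**The case against.** The strongest reply is that this is a condensed article and the platform may contain a random element that the text omits. That is possible. A reader might infer that the trial is not randomised at all; the document does not support going that far. It supports saying that the rule as published has no random element between control and programme. This is not a detail left to a fuller document, however: the article does state a mechanism, and that mechanism conflicts with its own description as random. A versus B may also still be random if ties are broken by chance, although the article does not say so.

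A second reply is that access is narrow: one researcher, on request, control versus intervention only. This stands as a limit. A reader might infer that enrolling staff can steer patients into arms, or that the group facilitators can predict the next placement. Nothing says that the researcher with access screens or enrols, and nothing gives facilitators the control counts or the order of entry. Selection bias is therefore possible but not shown. What remains is that the permitted view is exactly the information needed for prediction.

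Thirdly, registration during the baseline assessment and enrolment after it may be separate steps. Section 2.11 has blinded evaluators do the baseline assessments, and section 2.12.1 has the app installed afterwards. The order is therefore unclear and needs reconciling; it is not shown to be wrong.

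Finally, the sentence guaranteeing an even distribution most naturally means arm sizes, which the shortfall readings do deliver. It should not be read as a claim of prognostic balance.

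**Conclusion.** The point holds. The stated mechanism contradicts the claim of random assignment in the same section, and no other section supplies the missing chance element. Control versus programme is determined by past counts at about 96%, 98% or 100% of the 172 entries, depending on the shortfall reading. Hiding the screen therefore does not by itself secure concealment, and the reliance on random assignment in section 6 is not met by the rule as written.

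This rests on reading the distance from target as a shortfall, on the stated targets, and on the platform doing what the article says.

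Two further inferences are not supported. The first entrant is not always a control: under the share-filled reading, entry 1 is a three-way tie and was a control in about one third of runs. Nor do the documents give any basis for putting a size on the resulting bias.

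**What to change.** Replace the rule in section 2.8 with a concealed, computer-generated allocation list held in the platform. One workable form is permuted blocks in random order, with sizes not disclosed to staff: twelve blocks of 7 at A:B:control = 2:2:3 and eight blocks of 11 at 3:3:5. Check: 12×7 + 8×11 = 84 + 88 = 172; A = 24 + 24 = 48; B likewise 48; control = 36 + 40 = 76. Other schemes with a stated random element would also answer the point. If the platform already has such an element, describe it and correct the sentence.

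Release each assignment only when all baseline measures are complete, and reconcile the timing in sections 2.8 and 2.10 accordingly. State that nobody who screens or enrols may see past placements.

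**Cost.** A small platform change and revised wording, with no extra participants. Arm counts may drift slightly within a block. Some predictability remains if block sizes and boundaries become known: about 67% correct control/programme guesses in simulation, against 55.8% under simple randomisation and about 98% or more under the stated rule.

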### 2.9. Concealment Mechanism

Allocation will be concealed through the IDEApp web-based system and will be accessible only by request. In order to maintain allocation concealment, only one of the researchers in charge of the evaluation will be able to see the allocation placement. The allocation information will enlighten whether participants have been allocated to the control or intervention condition, but this study researcher will not know which of the experimental conditions (A or B) participants have been allocated to. The purpose of knowing the placement of participants is to inform them whether they must attend the IDEA group sessions or not.

### 2.10. Implementation

Allocation and intervention assignment will be automatically generated by the IDEApp web-based platform once participants are registered in the system by study staff. A study psychologist will enrol participants in the trial after baseline assessment.

### 2.11. Blinding

For logistics purposes, after assignment to study conditions, trial participants will know whether they have been allocated to experimental or control conditions, but the specific experimental intervention (A or B) will not be revealed. Unfortunately, it is hardly achievable to blind therapists and physiotherapists delivering the group sessions. Evaluators blind to treatment condition will carry out baseline assessments. To avoid assessment bias, an independent evaluator blinded to group allocation will complete follow-up assessments. Other care providers (i.e., clinicians), statisticians and principal investigators will be blind to randomisation procedure and group allocation.

Due to ethical considerations, the blinding process will be interrupted if a risk situation is detected during any phase of the study. In this case, the subject will be identified, and their clinician will be informed immediately. Cessation of participation will be discussed depending on the circumstances.

### 2.12. Data Collection and Management

#### 2.12.1. Plans for Assessment and Collection of Outcomes

A trained psychologist ([name]) and a physiotherapist ([name]) will carry out the assessments. Evaluation instruments have been described in the Outcomes section, and time points and assessment tools are outlined in Table 2.

Following referral, participants will attend the study entry clinical interview and baseline assessment, followed by an evaluation with a physiotherapist to identify their physical needs and capabilities. Such assessments will allow for the subsequent prescription of tailored exercise to the intervention groups. After baseline assessment, the study staff will install IDEApp on the smartphone of all participants and provide them with the smart band. Instructions on how to use both will be provided, alongside written information with basic information and contact information (e.g., help phone or email) where technical issues regarding device use will be resolved. In the first week after study entry, all subjects will effectively start using the devices and IDEApp, which will provide estimates of their baseline physical activity and exercise, and up until the end of the trial by implementing ecological momentary assessment methods (EMA). This monitoring system using a wearable band and a mobile phone-based EMA includes objective measures of physical activity and health variables, such as heart rate, walking and sleep patterns, and is intended to be minimally invasive to the users and their mobile phone usage. The EMA methods are expected to provide with accurate data on activity changes that will allow for adapting motivational messages according to the activity states.

After completion of the group sessions (or after 1 month for Control Group), every participant will be followed-up for eight months. Post-allocation assessments following the intervention at 4 weeks (T1) and 12 weeks (T2) will be carried out by telephone in order to ease the burden of participants. These assessments will last 30 min and will be performed from the facilities of the Centre Fòrum in order to guarantee data safety. The final assessment at 36 weeks (T3) will be carried out face-to-face and will follow a similar outline as the baseline assessment, and again will be carried out by a psychologist and a physiotherapist.

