### 2.5. Outcomes

#### 2.5.1. Primary Outcome Measure

Given the great heterogeneity expected in the sample of patients, the intervention is aimed at improving global functioning in the first place. The functional impairment will be assessed using the 36-item Short-Form Health Survey (SF-36v2, Quality Metric Inc., Lincoln, NE, USA) [13,14]. As the main target of the trial is to learn about the efficacy of personalised exercise prescription, the main outcome comparison will be (Intervention A + Intervention B) vs. Control, being the comparison of A vs. B vs. C considered as secondary.

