#### 2.12.2. Plans to Promote Participant Retention and Complete Follow-Up

The plans to promote participant retention and complete follow-up include: (1) delivering hand-outs with highlights at the end of each session; (2) contacting participants when no records of the smart band are detected by the IDEApp web-based platform; (3) contacting participants to remind them about the upcoming appointments and let them know what to expect from them and the estimated time frame; (4) availability and flexibility of study stuff to arrange assessment visits at convenient times; (5) developing good therapist–client alliance.

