### 3.2. Methods in Analysis to Handle Protocol Non-Adherence and Any Statistical Methods to Handle Missing Data

Last Observation Carried Forward analysis will be used to handle and minimise missing data on the clinical variables.

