**Figure 2 ijerph-18-06306-f002:**
[figure not shown]
Screenshots of IDEApp running on a smartphone (messages in Catalan). (**A**)—login and register screen; (**B**)—home Screen without notification; (**C**)—home screen with motivational notification.

**Table 1 ijerph-18-06306-t001:** Description of the content of the IDEA group sessions.

Session
1 Depression and exercise
2 Motivation towards exercise
3 Introduction to the exercise prescription
4 Barriers to exercise
5 Review of the exercise on prescription
6 What now? Exercise maintenance

**Table 2 ijerph-18-06306-t002:** SPIRIT diagram of the IDEA trial.

	Study Period					
	Enrolment	Allocation	Post-Allocation			Close-Out
Time point	−*t*_1_	*t* _0_	4 Week group sessions	*t* _1_	*t* _2_	*t* _3_
Enrolment:						
Eligibility screen	X					
Informed consent	X					
Allocation		X				
Interventions:						
Intervention A			X	X	X	X
Intervention B			X	X	X	X
Control group				X	X	X
Assessments:						
Sociodemographic data		X				
Health habits and clinical data		X				
SF-36		X		X	X	X
WHO-5 WBI		X		X	X	X
PHQ-9		X		X	X	X
SIMPAQ		X		X	X	X
6 min walking test		X				X
1 min STS test		X				X
Hand grip strength test		X				X
EMI-2		X				
Activity and sleep monitoring		X	X	X	X	X
Delivery of motivational messages				X	X	X

SPIRIT = Standard Protocol items: Recommendations for Interventional Trials [29].; *t*_1_ = pre-allocation; *t*_0_ = baseline assessment; *t*_1_ = post-allocation assessment at 4 weeks; *t*_2_ = post-allocation assessment at 12 weeks; *t*_3_ = final assessment at 36 weeks; SF-36 = 36-item short-form health survey; WHO-5 WBI = world health organization well-being index; PHQ-9 = patient health questionnaire; SIMPAQ = simple physical activity questionnaire; STS = sit-to-stand; EMI-2 = exercise motivations inventory.

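### The week-36 questionnaires, including the SF-36, are tied to a face-to-face visit that only three performance tests need; a telephone fallback would be a cheap improvement

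*Protocol article*

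**What the plan says.** Section 2.5.1 names the primary instrument: "The functional impairment will be assessed using the 36-item Short-Form Health Survey". It names no primary time point. The main comparison is A + B against control, which by section 2.1 is 48 + 48 = 96 against 76.

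Section 2.12.1 fixes the mode at each follow-up. The assessments "at 4 weeks (T1) and 12 weeks (T2) will be carried out by telephone in order to ease the burden of participants", and last 30 minutes. For week 36 the text is: "The final assessment at 36 weeks (T3) will be carried out face-to-face and will follow a similar outline as the baseline assessment". A psychologist and a physiotherapist carry out that visit.

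Table 2 schedules the SF-36, WHO-5, PHQ-9 and SIMPAQ at baseline and at all three follow-ups. The 6-minute walk, sit-to-stand and handgrip tests appear at baseline and week 36 only. EMI-2 appears at baseline only.

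Section 2.12.2 lists the retention measures. The one that concerns attendance directly is "availability and flexibility of study stuff to arrange assessment visits at convenient times"; appointment reminders are another. Completing a missed assessment remotely is not among them.

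Section 3.2 sets the missing-data rule: "Last Observation Carried Forward analysis will be used to handle and minimise missing data on the clinical variables".

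**The concern.** Every questionnaire that has a follow-up is taken by telephone twice before week 36, so a remote procedure is already in place. The stated reason for using it is participant burden. At the longest follow-up the plan moves the same questionnaires to the most burdensome type of contact, because they share a visit with three secondary tests that cannot be done by telephone. If the rule is followed literally, someone who would answer a call but will not travel loses the week-36 SF-36 as well as the performance tests.

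LOCF then substitutes a value that differs in time (week 12 or earlier) and in mode (telephone, unless it is the baseline value). The week-36 comparison becomes a mixture of long-term and shorter-term status, in a trial that aims to prolong benefit. A better imputation method would not recover answers that a call could have obtained, so this is a data-collection matter separate from the choice of LOCF.

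**Working it through.** **Inputs.** Section 2.6: d = 0.5, power 0.80, alpha 0.05, expected drop-out 20%. Section 3.1: two-sided testing. Section 2.1: 96 (A + B) and 76 (control).

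**The plan's own figure.** Normal approximation: n per arm = 2 × ((1.960 + 0.842)/0.5)² = 62.8, rounded up to 63. Inflated by 20%: 63 × 1.2 = 75.6, rounded up to 76, so 152 in two arms. This matches section 2.6. The added 20 participants give 172.

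**Assumption.** Let m be the share with no week-36 value, equal in both arms. The documents give no rate of missed T3 visits. The 20% is drop-out and serves here only as a reference point.

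**Power on observed week-36 values** (two-sample t-test, noncentral t, d = 0.5):

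| m | n (A + B / control) | Power |
|---|---|---|
| 0 | 96 / 76 | 0.90 |
| 10% | 86.4 / 68.4 | 0.87 |
| 20% | 76.8 / 60.8 | 0.82 |

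This shows the information lost. It does not describe the planned analysis, which is intention to treat with LOCF.

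**Effect under LOCF.** All 172 stay in the analysis and the expected estimate is (1 − m) × d36 + m × d_carried, where d36 is the true week-36 effect and d_carried the effect shown by the carried values. With m = 20% and d36 = 0.5:

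| d_carried | Estimate | Power (96 vs 76) |
|---|---|---|
| 0.50 | 0.8 × 0.5 + 0.2 × 0.50 = 0.50 | 0.90 |
| 0.25 | 0.8 × 0.5 + 0.2 × 0.25 = 0.45 | 0.83 |
| 0 (baseline carried) | 0.8 × 0.5 + 0.2 × 0 = 0.40 | 0.74 |

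The last row would need every non-attender to have missed both telephone assessments as well.

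The error can also go the other way. If the effect has faded to 0 by week 36 but the carried values show 0.5, the estimate is 0.2 × 0.5 = 0.10 at m = 20%, and 0.1 × 0.5 = 0.05 at m = 10%.

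**The case against.** The text does not say that T3 is face-to-face only, or that the questionnaires are forgone when someone cannot attend. The article is condensed, and the full protocol may contain a fallback. Section 2.4.1 also commits in general terms to adapting trial processes under COVID-19. This stands as a limit on the point: exclusivity is an inference from an unqualified statement of mode and a retention list without a remote option. It does not remove the point, because the article does fix the mode at each time point.

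The visit also has a reason: the performance tests need it, and T3 mirrors the baseline assessment. That is right, and nothing here argues against the visit itself.

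A reader might draw three stronger conclusions that the documents do not support.

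- **That non-attenders lose the primary outcome.** They lose one of three follow-up SF-36 measurements. No primary time point is named, and weeks 4 and 12 are kept.
- **That the fallback recovers a known share of a 20% loss.** The 20% is expected drop-out, which includes people who withdraw and would not take a call. No recovery rate is given. Those for whom baseline would be carried forward have already missed two telephone assessments, so another call is least likely to reach them.
- **That attendance will differ by arm and bias the main comparison by a stated amount.** Loss of 12% against 30%, with non-attenders differing by 0.5 SD, would give 0.5 × (0.30 − 0.12) = 0.09 SD. The split and the gap are both assumed, and the sum is for a completer analysis that is not planned. Participants do know whether they are experimental or control (section 2.11), and the programme arms attend six sessions at the centre. But those sessions end after one month, and both arms have the same calls, app, band, reminders and flexible visit times. A difference is possible; its size is unknown.

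**Conclusion.** The point holds as a cheap improvement, not as an error. Read as written, the plan ties the week-36 SF-36 to a visit that only three secondary tests require, and LOCF then fills a missed visit with an older value, usually taken in another mode.

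The benefit of a fallback is modest. Even with 20% of week-36 values missing, observed-case power at d = 0.5 is 0.82, above the planned 0.80. Under LOCF at that rate the loss runs from nothing, if the week-12 effect equals the week-36 effect, to an estimate of 0.40 with power 0.74 in an unlikely worst case. The better argument is that fewer week-36 values would be substitutes for earlier ones. All figures assume equal missingness across arms and a missed-visit rate that the documents do not give. Priority: could be changed.

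**What to change.** Amend the T3 sentence in section 2.12.1. The assessment is face-to-face where possible. If a participant does not attend within the T3 window, the blinded evaluator completes the SF-36, PHQ-9, WHO-5 and SIMPAQ by telephone with the procedure used at weeks 4 and 12. Only the three performance tests are then missing. Record the mode of completion and add a sensitivity analysis by mode.

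The cost is one sentence, one REDCap field and about 30 minutes of telephone time per non-attender, with staff and procedures already in place. The downside is mixed modes at week 36 for a minority of participants, possibly unevenly across arms, which is why the mode should be recorded and examined. If the full protocol already contains such a fallback, no change is needed beyond making sure the mode is recorded.
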